### Objective 3. Measure the impact of the KT on coverage and attitudes about immunisation

#### Focus groups to identify strategies

After the preliminary analysis, field teams will return to the communities to hold gender stratified focus groups. Key findings from the household interviews will be shared with the groups to generate additional insights, including how best to let similar communities know about the findings. Focus groups typically involve 8–12 participants. In a quiet location, groups are limited to a maximum of one hour in recognition of the value of participants' time. Participants are reassured about confidentiality (no identifiers are recorded). A trained facilitator runs the group, prompts to provoke discussion, and encourages participants to express opinions. A second member of the team records the content and manages the time.

##### Communications

Communication strategies (see below) to share the outcomes of the measurement with stakeholders in the intervention communities will be heavily conditioned by the outcome of the focus groups. The core concept is to socialise the household cost-benefit equation. Strategies are likely to include work with local elected representatives, community and religious leaders, service workers and community action groups such as citizen community boards (CCBs)[34].

###### Repeat survey

Each year for three years, the measurement will be repeated in both intervention and control sites. Much of the key instrument content will be unchanged, to detect time trends. Responses will provide substrate for the next round of household cost-benefit equations and cost-gain analysis, which in turn will feed into the next round of intervention.

### Objective 4. Develop an *evidence-based and gendered systems approach to increasing equity in immunisation*, rooted in community knowledge, capable of building on local health protection cultures and of informing evidence-based decision-making to improve the health of populations and strengthen health systems through immunisation services

A lot of effort has gone into the supply side of immunisation (vaccine purchase, training health workers and logistics). There is a need to focus systematically on the *demand *for immunisation – which is probably a direct function of the quality of information people have.

Parallel to the community-based knowledge transfer intervention, the team will work with the district authorities in Lasbela. We will build capacity to improve immunisation rates in the selected district, reaching health care workers, community leaders and policy makers. Research teams will be trained in community-based research, enhancing the capacity for ongoing monitoring of immunisation and other key public services.

The cost-gains approach offers a bridge between planner and community views. Proving the value of this parameter could support a paradigm shift in resource allocation, from a system based on reconciliation of competing sectoral claims without a comparable evidence base to cost-gain planning.

The main selling point of a new knowledge transfer approach to sustainable immunisation is that it must work. immunisation coverage must increase measurably and people in key positions must know about this. Mainstreaming the household cost-benefit equation begins with respectful dialogue with local health and political authorities about immunisation concepts, service delivery, effects and side effects in the communities. The central activity is then to demonstrate by measuring and communicating, in reiterative cycles, the effect on cost and benefit assessments. Comparisons between sites with different levels or types of intervention will be almost as informative as the longitudinal picture emerging by following each site over four years. Evaluation is thus built into the project.

In addition to the overall concept of evidence-based immunisation support, and the household cost-benefit equation, relevant procedures and tools include:

1. Protocols for the survey (household beyond-KAP, key informants and institutional review) and sample selection, processing results through double data entry, epidemiological analysis and interpretation in community-based focus groups;

2. Procedures for achieving policy level buy-in, including aggregation tools (like customised epidemiological mapping freeware) that allow compounding of local experiences into regional and national pictures; a menu of methods and practical examples of communication tools for opening evidence-based dialogue that can increase community ownership of immunisation.

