**Methods/design:**

In 32 communities representative of Lasbela district, 3344 households participated in a baseline survey on early child health. In the 18 randomly selected intervention communities, we will stimulate discussions on the household cost-benefit equation, as measured in the baseline. The reference (control) communities will also participate in the three annual follow-up surveys, feedback of the general survey results and the usual health promotion activities relating to immunisation, but without focussed discussion on the household cost-benefit equations.

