Current devolution reforms in Pakistan are expected to make service delivery more effective and to support institutionalised participation of community members[8,9]. Service delivery is now a district function, yet the provinces are still responsible for planning and monitoring health services [9]. The expanded programme of immunisation (EPI) remains a federal responsibility. The 2002 Pakistan Integrated Household Survey claimed an increase in immunisation coverage, mostly in the urban areas. The proportion of fully immunised children aged 12–23 months rose from 49% to 53%, and even this small gain was not consistent countrywide. In Balochistan, where the project will be located, immunisation coverage fell from 34% in 1998–9 to 24% in 2000–1, mostly attributed to diversion of resources to the polio eradication campaigns[10].

Balochistan is Pakistan's largest province (347,000 km^2^) and has the lowest population density (6.5 million, 19/km^2^). It covers more than 40% of the land area, but has less than 5% of the national population. The disease burden in Pakistan is still largely poverty-related, much of it preventable by immunisation[11,12].

Lasbella, in the south of Balochistan is one of the province's poorest districts. In 2003 there were around 50,000 women of childbearing age in this district. There were 11,594 infants under the age of one year, and reflecting the very high infant mortality, 8,140 children aged 12–23 months. The new district administration employs 39 full time vaccinators, but still only achieves symbolic coverage. The problem does not appear to be one of supervision or management. The vaccinators report to a superintendent, who in turn reports to the Deputy District Health Officer, who reports to the Executive District Officer for Health.

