#### Randomisation

From the latest Pakistan census, 32 enumeration areas were randomly selected to represent the population of Lasbela district. Once the baseline survey was completed, clusters were randomised into intervention and control, with precautions about the usual biases of this design[21]. In each cluster, interviewers contacted homes of 100 children under the age of 24 months of age (a total of 3344 households). Three successive cycles that examine successive cohorts of children in this age group, and the same number of households in each site (not necessarily the same households) will preserve the proportional representation.

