## Discussion

Engagement of communities in evidence-based planning is a novel approach to immunisation, an intervention driven perhaps more than any other by an inappropriate if well-intentioned ethos of "we know what is good for you". The idea of a household cost-benefit equation is common sense: people weigh things up before their health choices. This study hopes to answer questions about what it takes to enter a dialogue that influences these equations. The year-to-year shift in knowledge, attitudes, subjective norms, intention, sense of agency, ability to discuss, and ultimately, uptake of immunisation will be evident from the results of the successive cycles.

Best practice cases – communities that increase immunisation – will be identified and held up as positive examples of what is possible under prevailing conditions. The direct beneficiaries will be the public, but indirect beneficiaries will be planners and policy-makers in federal, provincial and district governments. Improved understanding of immunisation risks and cost implications of higher immunisation uptake may be applicable in many other countries. Proof of cost-gains as the planners' corollary of the household cost-benefit equation could open new horizons for evidence-based service-public interaction.

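### Objective 4 ranks change over time within sites above comparison between sites, which conflicts with the randomised design and the planned intervention-versus-reference analysis

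*Protocol article*

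**What the plan says.** Under Objective 4, in the paragraph on mainstreaming the approach, the article states: "Comparisons between sites with different levels or types of intervention will be almost as informative as the longitudinal picture emerging by following each site". The follow-up it refers to spans four years. The next sentence concludes: "Evaluation is thus built into the project".

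Other sections describe a randomised comparison:

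- Randomisation: "Once the baseline survey was completed, clusters were randomised into intervention and control".
- Abstract, Methods/design: "In the 18 randomly selected intervention communities, we will stimulate discussions on the household cost-benefit equation, as measured in the baseline". With 32 communities in all, 14 are reference communities.
- Analysis (Objective 2): intervention and reference sites are compared by Mantel-Haenszel methods, reported as an odds ratio or risk difference. Independence from age, sex, household employment, community size, remoteness and other factors is examined.
- Repeat survey (Objective 3): both arms are measured each year for three years.

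Three further statements bear on how trends can be read. Background reports that in Balochistan "immunisation coverage fell from 34% in 1998–9 to 24% in 2000–1", mostly attributed to resources going to polio campaigns, and that national full immunisation rose from 49% to 53%. Objective 4 adds capacity building with the district authorities, alongside the community intervention. Communications (Objective 3) makes the form of communication in the intervention communities depend on the focus groups.

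**The concern.** In a cluster-randomised trial, the contrast between arms at the same time is what separates the intervention from everything else that changes. The Objective 4 sentence puts the picture over time first and the comparison between sites a close second, and then calls this the evaluation.

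A rise within intervention communities could come from the intervention, from district-wide capacity building, from service reform or from a vaccination campaign. A fall could hide a real benefit. Comparing intervention communities by the level or type of activity they had does not solve this, because that variation is shaped locally and is not allocated at random.

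At stake is what may be claimed. The results are meant to persuade planners that the approach works, and the Discussion intends to hold up communities whose coverage rises as examples. If the text leaves open which evidence decides impact, a background trend can be credited to the intervention or counted against it.

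**Working it through.** The article gives no power, alpha or ICC figure on this point, so there is no stated result to reproduce. The steps below show how far a trend within sites can mislead.

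**1. What each comparison estimates.** Let E be the intervention effect, S the secular change and D the effect of district-wide work.

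- Change within intervention sites: E + S + D.
- Change within reference sites: S + D, assuming both arms are reached alike.
- Difference between arms at the same survey: E, because randomisation balances the rest in expectation.

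**2. Size of S in the document's own figures.**

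- Balochistan: 24 − 34 = −10 points. Odds ratio = (0.24/0.76)/(0.34/0.66) = 0.61.
- National: 53 − 49 = +4 points.
- Lasbela coverage is about one in ten (Abstract). A secular rise with the inverse odds ratio, 1/0.613 = 1.63, gives odds 0.111 × 1.63 = 0.181, which is 15.3%.

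**3. Chance that a before-after test in the 18 intervention sites is significant when E = 0.**

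Inputs: the Randomisation section reports that "interviewers contacted homes of 100 children under the age of 24 months of age (a total of 3344 households"), so the mean is 3344/32 = 104.5 per cluster and 18 × 104.5 = 1881 households per round, if evenly spread. Assumed: two-sided alpha 0.05, ICC from 0 to 0.20, rounds treated as independent.

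Design effect = 1 + (104.5 − 1) × ICC. Effective n = 1881 / design effect. Probability = Φ[(|p1 − p2| − 1.96 × SE0)/SE1], with SE0 from the pooled proportion and SE1 from the separate proportions.

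| ICC | Design effect | Effective n | 34% to 24% | 10% to 15.3% | 49% to 53% |
|---|---|---|---|---|---|
| 0 | 1.00 | 1881 | >0.99 | 0.999 | 0.69 |
| 0.01 | 2.04 | 924 | 0.997 | 0.93 | 0.41 |
| 0.05 | 6.18 | 305 | 0.78 | 0.51 | 0.17 |
| 0.10 | 11.35 | 166 | 0.52 | 0.31 | 0.11 |
| 0.20 | 21.70 | 87 | 0.30 | 0.18 | 0.08 |

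Every entry exceeds the nominal 0.05. Returning to the same communities would recover some precision, which would make a secular shift easier to detect and so raise these probabilities.

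**4. Following single sites.** With 104.5 households per round and 10% coverage, the standard error of one site's change is √(2 × 0.1 × 0.9/104.5) = 0.042, or 4.2 points. With no true change anywhere, about half the sites would rise by chance. A best-practice community chosen for its own rise is weak evidence.

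**The case against.** The strongest reply is that the analysis is settled elsewhere. The Analysis section plans the intervention-versus-reference comparison and the Repeat survey section keeps the reference sites under measurement. The Objective 4 sentence stands in a paragraph on promoting the approach. It sets no test, estimand or decision rule, and no section plans a before-after test of effect. This stands, and it is why the point is minor. It does not remove the contradiction, because the sentence is followed directly by the statement that evaluation is built in.

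Four stronger readings are tempting, and the document does not support them:

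- *That the plan treats uncontrolled trends as its most informative evidence.* The sentence compares two sources with each other only. Following each site also includes the reference sites, so a controlled difference in change is available.
- *That the randomised contrast is left out.* Reference communities receive survey feedback and usual promotion, so sites with different types of intervention can mean the two arms. On that reading the randomised contrast is present but ranked second.
- *That communities select their own level of intervention according to willingness to immunise.* No section says so. The text supports only that communication is shaped by focus groups, so variation within the arm is not randomised.
- *That even a 2-point drift would look highly significant.* For the 18 intervention sites the standard error ignoring clustering is √(0.18/1881) = 0.98 points, so z = 2/0.98 = 2.04. At an ICC of 0.05 it is 0.98 × √6.18 = 2.43 points and z = 0.82.

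The Discussion also says: "The year-to-year shift in knowledge, attitudes, subjective norms, intention, sense of agency, ability to discuss, and ultimately, uptake of immunisation will be evident" from successive cycles. That is descriptive and attributes nothing to the intervention.

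**Conclusion.** The point holds in limited form, as a minor one. Objective 4 ranks change within sites above comparison between sites as the project's evaluation, which conflicts with the randomised allocation and with the article's own Analysis section. The sentence fails on either reading: it places the randomised contrast below the time trend, or it relies on variation within the intervention arm that was not randomised.

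The possible error is not negligible. A background shift like the provincial one would give a false before-after result with probability 0.30 to 0.78 for ICCs of 0.20 to 0.05; the smaller national shift gives 0.08 to 0.17. These figures rest on an assumed alpha, ICC and even spread of households. They also borrow provincial and national changes, which are not Lasbela data; the provincial fall has a stated cause. They illustrate what reliance on trends would risk, and do not show that the planned comparison between arms is biased.

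**What to change.** Reword the Objective 4 sentence so that impact is judged by the concurrent difference between the 18 intervention and 14 reference communities, each analysed in the arm to which it was randomised. Add cluster-level baseline uptake by name to the adjustment factors in the Analysis section. It was measured before allocation and can improve precision.

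Present trends within sites, comparisons by level or type of intervention, and best-practice cases as descriptive. Show the reference-arm trend beside them and draw no causal claim from them.

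The cost is wording and one extra covariate, with no new data. The downside is that fewer positive statements can be drawn from trends alone.

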## Discussion

Engagement of communities in evidence-based planning is a novel approach to immunisation, an intervention driven perhaps more than any other by an inappropriate if well-intentioned ethos of "we know what is good for you". The idea of a household cost-benefit equation is common sense: people weigh things up before their health choices. This study hopes to answer questions about what it takes to enter a dialogue that influences these equations. The year-to-year shift in knowledge, attitudes, subjective norms, intention, sense of agency, ability to discuss, and ultimately, uptake of immunisation will be evident from the results of the successive cycles.

Best practice cases – communities that increase immunisation – will be identified and held up as positive examples of what is possible under prevailing conditions. The direct beneficiaries will be the public, but indirect beneficiaries will be planners and policy-makers in federal, provincial and district governments. Improved understanding of immunisation risks and cost implications of higher immunisation uptake may be applicable in many other countries. Proof of cost-gains as the planners' corollary of the household cost-benefit equation could open new horizons for evidence-based service-public interaction.

